(Group D – vaccination and sampling schedule in Table 2), by administration of a single dose of oral azithromycin 28 days prior to receiving LAIV. This timeframe has been chosen based on pilot data from the the Gambia showing significant alternation in the nasopharyngeal microbiome approximately 1 month after single dose oral azithromycin in Gambian children aged 1 – 7 years in mass trachoma treatment campaigns ([name], unpublished, personal communication). These subjects will be matched as closely as possible by pre-antibiotic nasopharyngeal microbiome profile [1], age (24 – 35, 36 – 47, 48 – 59 months) and sex (in that hierarchical preference), in a nested case-control study, to n = 35 children recruited in the main clinical trial. This will be done after all children have been recruited and microbiome sequencing and analysis has been completed. To avoid allocation bias of these controls, an individual in the [name] laboratory blinded to the immunogenicity data will undertake this matching process. In brief, the microbiome profile matching will be performed by first categorizing which of eight described profiles each child's microbiome clusters with depending on the dominant taxa (e.g. *Staphylococcus*, *Streptococcus*, *Moraxella* etc.) as described previously by the [name] group [1].

The day 2 visit window for groups A, B and D is deliberately restrictive to allow both blood and NPS to be taken at a time when peak gene expression changes post-LAIV can be captured. The other visit windows are intentionally liberal to maximize the opportunity to obtain a full set of blood and NPS samples for the purpose of the analysis, whilst in each case, not compromising the scientific objectives they are designed to deliver. However, in each case, the intention will be to obtain the sample on or as close to the day specified as possible. The sampling schedule and associated laboratory assays to be performed on each clinical sample is detailed in Table 3. The procedure to deal with participants who default visit windows is discussed in section 5.4.

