### **55**    Exclusion criteria

No subject being initiated on the study protocol may have any of the following exclusion criteria at study entry:

- Serious, active, medical condition, including but not limited to:
  - chronic disease of any body system
  - severe protein-energy malnutrition (weight-for-height Z-score of less than -3)
  - known genetic disorders, such as Down's syndrome or other cytogenetic disorder
- Active wheezing
- History of documented hypersensitivity to eggs or other components of the vaccine (including gelatin, sorbitol, lactalbumin and chicken protein), or with life-threatening reactions to previous influenza vaccinations.
- History of documented hypersensitivity to macrolide antibiotics
- History of Guillain-Barré syndrome.
- Receipt of aspirin therapy or aspirin-containing therapy within the two weeks before planned study vaccination.
- Any suspected or confirmed congenital or acquired state of immune deficiency including but not limited to primary immunodeficiencies including thymus

disorders, HIV/AIDS, hematological or lymphoid malignancies (blood tests will not be routinely undertaken with this regard as part of the study).

- Any current immunosuppressive/immunomodulatory treatment or receipt of any such treatment within the six months preceding trial enrolment (for corticosteroids this is defined as a dose of prednisolone (or equivalent) of greater than 2mg/kg/day for one week or 1mg/kg/day for one month. The use of topical corticosteroids is not an exclusion criterion.
- The use of inhaled corticosteroids within the last one month.
- Receipt of an influenza vaccine within the past 12 months.
- Has any condition determined by investigator as likely to interfere with evaluation of the vaccine or be a significant potential health risk to the child or make it unlikely that the child would complete the study.
- Any significant signs or symptoms of an acute illness or infection including:
  - an axillary temperature of 38.0°C or above or documented fever of 38°C or above in the preceding 14 days.
  - Any acute respiratory infection within 14 days of enrollment visit.

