## **58 Missed visit windows and criteria for withdrawal**

Subjects that miss visit windows will continue on the study protocol and all procedures relevant to the *subsequent* visit undertaken as planned at the correct time. Samples for the missed visit window will *not* be collected. Samples that have already been collected will still be used for inclusion in analyses addressing relevant objectives.

In the event that subjects receive unplanned antibiotic therapy after commencing the study but prior to their planned final visit (i.e. the day 21 visit), the subjects will be excluded from analyses of primary objectives relating to nasopharyngeal microbiome changes. Samples collected will still be included in analyses relating to other objectives.

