### **72 Medical and drug history**

A medical history will be obtained by the investigator, sub-investigator or study nurse. Any abnormal findings requiring further treatment will be managed according to local practice or an appropriate referral made according to the nature of the condition. A lack of exclusion criteria will be confirmed.

All concomitant medications a child is receiving will be recorded in the CRF. Data on antibiotic use within the last month will also be collected and recorded. The use of concomitant medication, other than those considered exclusion criteria, does not preclude recruitment (see section 5.3.2).

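### The azithromycin contrast may be diluted, because comparators with recorded antibiotic use in the month before LAIV can be selected as matches

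*Combined protocol and SAP*

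**What the plan says.** Section 21 (Type of study and design) defines Group D by "administration of a single dose of oral azithromycin 28 days prior to receiving LAIV". The interval rests on pilot data showing "significant alternation in the nasopharyngeal microbiome approximately 1 month after single dose oral azithromycin". The 35 Group D children are to be "matched as closely as possible by pre-antibiotic nasopharyngeal microbiome profile", then by age band and sex, "to n = 35 children recruited in the main clinical trial". Matching happens after all recruitment and sequencing, by someone blinded to the immunogenicity data. No other matching factor is listed.

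On recent antibiotics, section 72 (Medical and drug history) says: "Data on antibiotic use within the last month will also be collected and recorded". It adds: "The use of concomitant medication, other than those considered exclusion criteria, does not preclude recruitment". Section 55 (Exclusion criteria) does not list antibiotic use. Its nearest item is "Any acute respiratory infection within 14 days of enrollment visit", with a parallel item for fever over the same 14 days.

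Three other places touch on the subject:

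- Section 58 (Missed visit windows) deals with unplanned antibiotics after study entry. It removes those children from the primary microbiome analyses only: "Samples collected will still be included in analyses relating to other objectives".
- Section 128 (Impact of LAIV on the nasopharyngeal microbiome) names antibiotic use in the last month as an adjustment factor for that analysis.
- Section 129 (Other statistical analyses) gives recent antibiotic use as an example of a baseline characteristic to compare between groups, and makes a general commitment to account for relevant covariates.

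**The concern.** The azithromycin comparison asks whether an antibiotic given about a month before LAIV changes nasal gene expression and the mucosal response. Its comparators should stand for children who had no such exposure. As the selection rule is written, a main-trial child who took an antibiotic in the month before day 0 is as eligible to be a comparator as one who did not.

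The plan's own reasoning makes this relevant. It expects one dose to leave a mark on the microbiome at about a month, and it treats antibiotic use in the last month as a confounder when it studies LAIV's effect on the microbiome. It does not carry that through to the one comparison in which an antibiotic is the intervention. If some comparators were exposed, the contrast would tend towards no difference, and a null result would be harder to interpret.

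**Working it through.** **Inputs from the documents**

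- 35 Group D children and 35 comparators (section 21); 30 v 30 for the microarrays (section 121).
- LAIV recipients with post-vaccination samples: Groups A and B, 110 each (Table 1). Day-2 nasal swabs are taken in both groups, day-2 blood in Group A only. Group C has no sampling after its LAIV dose.
- Profile categories: 8. Age bands: 3. Sexes: 2 (section 21).

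**Inputs that are assumed**

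- p, the share of comparators with an antibiotic in the month before day 0: 5% to 20%.
- f, the fraction of the azithromycin effect that this antibiotic produces: 0.5 to 1.

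**The plan's own figure.** Section 121 gives 30 per group so that at least 90% of 49,386 genes have at least 90% power at Bonferroni-corrected alpha 0.01 for a 2-fold change. This cannot be reproduced, because the gene-level standard deviations are not given. It can only be calibrated. With two-sided alpha = 0.01/49,386 = 2.02 × 10⁻⁷, a difference of 1 on the log2 scale, n = 30 and power 0.90, the implied SD is 0.528 (noncentral t). That calculation is for a generic two-group gene comparison, not specifically for azithromycin.

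**Dilution.** Observed difference = true difference × (1 − p × f). Effective n per group = 30 × (1 − p × f)². For a generic comparison with 80% power at two-sided 0.05, power = Φ(2.802 × (1 − p × f) − 1.960). The last column uses the calibrated SD.

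| p | f | Factor | Effective n (of 30) | Power, if 80% undiluted | Power, if 90% undiluted, Bonferroni |
|---|---|---|---|---|---|
| 5% | 0.5 | 0.975 | 28.5 | 78% | 87% |
| 5% | 1 | 0.95 | 27.1 | 76% | 83% |
| 10% | 0.5 | 0.95 | 27.1 | 76% | 83% |
| 10% | 1 | 0.90 | 24.3 | 71% | 74% |
| 20% | 0.5 | 0.90 | 24.3 | 71% | 74% |
| 20% | 1 | 0.80 | 19.2 | 61% | 50% |

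The factor column is the result that matters. The power columns only translate it: the plan states no power for the azithromycin contrast.

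**How many comparators.** The expected number exposed among 35 is 35p = 1.75, 3.5 and 7 at p = 5%, 10% and 20%. The chance of at least one, 1 − (1 − p)³⁵, is 83%, 97% and over 99.9%.

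**Pool after restriction.** There are 8 × 3 × 2 = 48 matching cells. Before restriction the average is 220/48 = 4.6 children per cell for nasal samples and 110/48 = 2.3 for day-2 blood. Removing 20% leaves 176/48 = 3.7 and 88/48 = 1.8. These are averages; real cells will be uneven.

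**The case against.** The strongest reply is that profile matching already controls most of the problem. The only pre-LAIV swab in Groups A and B is on day 0, so a comparator's profile is measured after any recent antibiotic. It is matched to a Group D child's profile from before azithromycin. A comparator moved into another profile by an antibiotic is therefore paired with a Group D child who had that profile anyway. At the level of the eight profiles this is the matching doing its work, and in the formula it lowers f. This stands in part. It does not reach differences within a broad profile, or effects of an antibiotic that do not run through the profile.

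Second, the data are collected, and section 129 permits both a baseline comparison and covariate adjustment. That is true, but the section does not name the Group D contrast and does not change the rule by which comparators are selected.

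Third, entry is limited to healthy children with no fever or acute respiratory infection in the previous 14 days. This plausibly lowers recent antibiotic use, but leaves the earlier half of the month uncovered and is not an antibiotic criterion.

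A reader might go further and infer that the contrast is diluted, or that it loses a known amount of power. The documents do not support that. They give neither p nor f, and no passage describes the comparators as free of antibiotics.

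**Conclusion.** The point holds as a possibility that the plan leaves open and could close cheaply. Exposed children can be selected as comparators, so the contrast may shrink by p × f: 2.5% to 20% over the assumed ranges. The true figure could be lower if use was rare or matching absorbs much of the effect. Equivalence to azithromycin (f = 1) is an assumption, and day-0 profile matching argues for something less.

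The reach is limited. This is exploratory objective (iv), in a non-randomised nested comparison. A reader might infer that the primary objectives are weakened or that the plan would declare modulation unimportant after a null result. Neither follows: the primary objectives do not use this contrast, and the plan has no decision rule attached to it.

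**What to change.** In section 21, add to the matching rule that comparators are drawn from LAIV recipients (Groups A and B) with no antibiotic recorded in the month before day 0, and that matching is done within that pool: up to 220 children for nasal samples, and up to 110 from Group A where day-2 blood is needed.

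For symmetry, apply the same item to Group D for the month before day −28, so that the profile used for matching really is pre-antibiotic, and for non-study antibiotics between day −28 and day 0. The minimum is a sensitivity analysis that excludes exposed children from both sides.

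If the restricted pool makes the profile match too poor, keep the full pool, adjust for recent antibiotic use as a named covariate in the Group D analysis, and report the analysis without exposed children as a sensitivity analysis. State in advance which route is primary and what would trigger the other.

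The change needs no new visit or sample. Recent use is already recorded at entry, matching has yet to happen when recruitment ends, and the rule in section 58 already presupposes that antibiotics taken after entry are known. The cost is a somewhat smaller pool and slightly less exact matches, felt most for day-2 blood. Excluding Group D children outright would also draw on the small margin between 35 enrolled and 30 needed for the microarrays, which is why a sensitivity analysis is the minimum asked there.

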**Table 1. Visit, vaccination and sampling schedule for groups A, B and C**

| Visit timing (from LAIV) | Visit window | Vaccinations and clinical samples | Group A (n = 110) | Group B (n = 110) | Group C (n = 110) |
|--------------------------|--------------|-----------------------------------|-------------------|-------------------|-------------------|
| Day 0 visit              | -            | Intranasal LAIV                   | X                 | X                 |                   |

|              |         |                                                           |             |             |            |
|--------------|---------|-----------------------------------------------------------|-------------|-------------|------------|
|              |         | Oral swab
NPS
Blood sample (5ml)                    | X
X
X | X
X
X | X          |
| Day 2 visit  | + 1 day | NPS
Blood sample (5ml)                                 | X
X      | X
-      |            |
| Day 7 visit  | +7 days | NPS
Blood sample (5ml)                                 | X
-      | X
X      | X          |
| Day 21 visit | +7 days | Oral swab
NPS
Blood sample (5ml)
Intranasal LAIV | X
X
X | X
X
X | X

X |

LAIV - live attenuated influenza vaccine; NPS - nasopharyngeal swab

**Table 2. Visit, vaccination and sampling schedule for group D**

| Visit timing  | Visit window | Vaccination,
antibiotics and
clinical sampling      | Group D (n = 35) |
|---------------|--------------|-----------------------------------------------------------|------------------|
| Day -28 visit | -            | NPS
Oral azithromycin                                  | X
X           |
| Day 0 visit   | +7 days      | Intranasal LAIV
Oral swab
NPS
Blood sample (5ml) | X
X
X
X |
| Day 2 visit   | + 1 day      | NPS
Blood sample (5ml)                                 | X
X           |
| Day 7 visit   | +7 days      | NPS                                                       | X                |
| Day 21 visit  | +7 days      | Oral swab
NPS
Blood sample (5ml)                    | X
X
X      |

LAIV - live attenuated influenza vaccine; NPS - nasopharyngeal swab

**Table 3. Sampling schedule and use of clinical samples in laboratory assays**

| Visit timing from LAIV
(window) | Clinical Sample | Laboratory assays                                                                                                                                                                                              |
|--------------------------------------------|------------------------|-----------------------------------------------------------------------------------------------------------------------------------------------------------------------------------------------------------------------|
| Day 0 visit                                | Oral swab              | Influenza-specific IgA and IgG                                                                                                                                                                                        |
|                                            | NPS^                   | Nasopharyngeal microbiome
Influenza-specific IgA
Host transcriptomic profiling
Viral multiplex RT-PCR                                                                                                        |
|                                            | Blood sample (5ml)     | Innate cell profiling (FC)
Influenza-specific T-cell responses (FC)
B-cell phenotyping (FC)
Peripheral T-follicular helper cells (FC)
Host transcriptomic profiling
Serum haemagglutination inhibition |
| Day 2 visit
(+ 1 day)                   | NPS                    | Host transcriptomic profiling
LAIV virus shedding (RT-PCR)                                                                                                                                                         |
|                                            | Blood sample (5ml)     | Innate cell profiling (FC)
Host transcriptomic profiling                                                                                                                                                           |

|                            |                    |                                                                                                                                                        |
|----------------------------|--------------------|--------------------------------------------------------------------------------------------------------------------------------------------------------|
|                            |                    | Host DNA extraction                                                                                                                                    |
| Day 7 visit
(+ 7 days)  | NPS^               | Nasopharyngeal microbiome
LAIV virus shedding (RT-PCR)                                                                                              |
|                            | Blood sample (5ml) | Peripheral T-follicular helper cells (FC)
Influenza-specific T-cell responses (FC)
B-cell phenotyping (FC)                                       |
| Day 21 visit
(+ 7 days) | Oral swab          | Influenza-specific IgA and IgG                                                                                                                         |
|                            | NPS^               | Nasopharyngeal microbiome
Influenza-specific IgA                                                                                                    |
|                            | Blood sample (5ml) | Peripheral T-follicular helper cells (FC)
Influenza-specific T-cell responses (FC)
B-cell phenotyping (FC)
Serum haemagglutination inhibition |

LAIV - live attenuated influenza vaccine; NPS - nasopharyngeal swab; RT-PCR – reverse-transcriptase polymerase chain reaction; IgA – immunoglobulin A, IgG – immunoglobulin G; FC - Flow Cytometry  
In addition, the nasopharyngeal swab from group D taken on the day -28 visit will be used for nasopharyngeal microbiome sequencing.

^NPS taken on days 0, 7 and 21 from group C will be used for nasopharyngeal microbiome sequencing

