## 20 Study design

### 21 Type of study and design

All primary objectives and most exploratory objectives will be addressed through the conduct of a phase 4, randomized, controlled clinical vaccine trial. A total of 330 healthy children aged 24 – 59 months will be enrolled into one of three groups of equal size (3 x 110 children):

- (i) LAIV-vaccinated (Group A - blood sample at day 0, 2, 21)
- (ii) LAIV-vaccinated (Group B - blood sample at day 0, 7, 21)
- (iii) Control group (Group C)

Allocation concealment will be maintained from the start through the use of sealed envelopes. Block randomization stratified by sex will be used and a randomization sequence will be generated by an MRC Statistician not involved in the study. Investigators will not be blinded to group allocation from this point onwards as the sampling schedule differs between groups. Local laboratory staff will therefore not be blinded for this reason, but samples sent to external laboratories will be blinded (see section 3.2.3).

Two LAIV-vaccinated groups are included in order to achieve several exploratory objectives, which require blood sampling at different time points following vaccination, whilst minimizing the number of times children are bled times (i.e. 2nd blood sample at either day 3 or day 7 post-LAIV, but not both). The unvaccinated subjects will serve as a control group for the primary objective of assessing the impact of LAIV on the nasopharyngeal microbiome. Section 8 details the statistical considerations made to decide on the sample sizes to be recruited. The vaccination and sampling schedules for groups A, B and C are detailed in Tables 1.

Group C subjects will be administered LAIV after the NPS is taken on their day 21 visit, to offer them the same level of protection against influenza illness by participating in the study as those in groups A, B and D.

An additional 35 healthy children aged 24 – 59 months will be recruited in the 2nd phase of recruitment (Jan – June 2018) to assess the objective of how modulation of the nasopharyngeal microbiome with antibiotics impacts the mucosal immunogenicity to LAIV

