Participants in groups A and B (n = 110 each) will be enrolled for approximately 4 –10 months: 21 days of active participation during recruitment months January – June 2017 or January – June 2018, followed by attendance at the Sukuta Health Centre for assessment of any ILI that occurs up to the 31st of October in the year of recruitment into the study. This design has been chosen as data from Senegal show that peak influenza transmission occurs between July and October each year ([name], XVII International Symposium on Respiratory Viral Infections, Vancouver, CA, 2015).

Group C will be enrolled for 21 days, with participation finishing following the day 21 visit and receipt of LAIV (Table 1). Group D (n = 35) will be enrolled for approximately 4 – 10 months: 49 days of active participation during recruitment months January – June 2018, followed by attendance at the Sukuta Health Centre for assessment of any ILI that occurs up to 31.10.18. Those individuals presenting with possible ILI will have a limited history taken and if a sudden onset of a fever of  $\geq 38^{\circ}\text{C}$  (axillary) *and* either a cough or sore throat is present, a nasopharyngeal swab will be taken and diagnostic viral rRT-PCR performed.

The vaccine to be studied (Nasovac-S) has a WHO pre-qualification certificate and marketing authorization for the study population. However, the trial will provide detailed information on the determinants of immunogenicity and therefore inform the design of future generations of similar live intranasal influenza vaccines.

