## **101 IFITM3 gene polymorphisms**

Genomic DNA will be extracted from an aliquot of whole blood (Table 3). DNA will be shipped frozen on dry ice to [name] laboratory in Oxford, who will perform genotyping of the IFITM3 rs12252 gene of all vaccinated subjects (n = 255) in the study for exploratory analyses to see whether polymorphisms in IFITM3-rs12252 impact on immunogenicity of LAIV. IFITM3 CC genotype is associated with greater expression of interferon-stimulated genes in wild-type pdmH1N1 infections and the 1000 genome project suggests a relatively high prevalence of this genotype in the Gambia at 21% ([name], personal communication). It is possible, therefore, that different innate immune responses to LAIV due to IFITM3 polymorphisms may account for differences in downstream adaptive immune responses.

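### Table 3 takes host DNA only from day 2 blood, which Group B does not give, so the written schedule supplies DNA from 145 of the 255 children to be genotyped for IFITM3

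*Combined protocol and SAP*

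**What the plan says.** Section 101 (IFITM3 gene polymorphisms) gives the source of the DNA: "Genomic DNA will be extracted from an aliquot of whole blood (Table 3"). It then gives the coverage: "genotyping of the IFITM3 rs12252 gene of all vaccinated subjects (n = 255").

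Table 3, which assigns assays to samples, shows "Host DNA extraction" once. It stands directly after the day 2 blood assays (innate cell profiling and host transcriptomics) and directly before the row labelled day 7. The day 0, day 7 and day 21 blood rows do not list it.

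Section 21 sets the bleeding days: "LAIV-vaccinated (Group A - blood sample at day 0, 2, 21") and "LAIV-vaccinated (Group B - blood sample at day 0, 7, 21"). Table 1 agrees, with a dash for Group B's day 2 blood. Table 2 gives Group D blood on days 0, 2 and 21 and only a nasopharyngeal swab on day 7.

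The day 7 blood row of Table 3 reads "Peripheral T-follicular helper cells (FC) Influenza-specific T-cell responses (FC) B-cell phenotyping (FC"). Exploratory objective (xi) in section 16 relates IFITM3 genotype both to early innate responses and to later influenza-specific responses.

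**The concern.** Section 101 relies on Table 3 for the DNA source, and Table 3 ties DNA to a draw that half of the randomised vaccinated children never give. A laboratory working from Table 3 would set aside no DNA aliquot for Group B, although section 101 counts those children.

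The loss would fall unevenly. Group B is the only group bled on day 7, so it is the only source of day 7 T-cell, pTfh and B-cell data. Those are among the later influenza-specific responses that objective (xi) is meant to relate to genotype. The aliquot also has to be set aside when the blood is processed, so an omission may be hard to repair afterwards.

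**Working it through.** **Inputs**
- Group sizes: "Participants in groups A and B (n = 110 each") from section 21; Group D, 35, from Table 2.
- Blood days: A 0, 2, 21; B 0, 7, 21; D 0, 2, 21 (section 21, Tables 1 and 2).
- Host DNA: day 2 blood (Table 3).
- CC genotype prevalence: 21% (section 101).
- Attrition allowance: about 10% (section 51).

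**1. The plan's own figure.** A + B + D = 110 + 110 + 35 = 255. This matches section 101 exactly. A + B alone gives 220, and all four groups give 365. Group C receives vaccine at its day 21 visit but gives no blood, so it is properly outside the 255. Group B is inside it.

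**2. Coverage under Table 3.** Groups with day 2 blood: A + D = 110 + 35 = 145. The shortfall is 255 − 145 = 110, which is all of Group B, and 110/255 = 43%. With 10% attrition in every group the comparison is 0.9 × 255 = 229.5 against 0.9 × 145 = 130.5.

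**3. Effect by outcome**

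| Outcome | Groups measured | Children measured | With scheduled DNA | Lost |
|---|---|---|---|---|
| Day 2 blood (innate cells, transcriptomics) | A, D | 145 | 145 | 0 |
| Day 7 blood (T-cell, pTfh, B-cell) | B | 110 | 0 | 110 |
| Day 21 outcomes | A, B, D | 255 | 145 | 110 |

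The counts are ceilings from the group sizes, before attrition and missed samples.

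**4. Precision for day 21 outcomes.** The plan gives no power, contrast or test for objective (xi), so this step is illustrative. Assume CC versus non-CC on a continuous outcome, 80% power, two-sided alpha 0.05, a normal approximation and no attrition:

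detectable difference in SD = 2.8 × √(1/(0.21n) + 1/(0.79n))

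- n = 255: 53.55 CC and 201.45 non-CC; 2.8 × √(1/53.55 + 1/201.45) = 0.43 SD.
- n = 145: 30.45 CC and 114.55 non-CC; 2.8 × √(1/30.45 + 1/114.55) = 0.57 SD.

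The ratio of standard errors is √(255/145) = 1.33 whatever the CC prevalence, provided it is the same in each group. With 10% attrition throughout, both figures are divided by √0.9, giving about 0.45 and 0.60 SD.

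**5. A wording slip that changes nothing here.** Section 21 also describes the second bleed as a "blood sample at either day 3 or day 7 post-LAIV, but not both". The tables say day 2 where this sentence says day 3. On either reading Group B has no early draw, and the counts stand.

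**The case against.** The strongest reply is that the intent is clear. Section 101 names every vaccinated child and its total counts Group B. Group B gives 5 ml of blood on days 0, 7 and 21, and a genotype does not depend on the day of the draw. On this view one table cell is incomplete and staff would take DNA from another tube. This stands as an account of intent and of feasibility. It does not supply the missing instruction: section 101 sends the reader to Table 3, and no other part of the protocol schedules DNA from a Group B sample.

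Second, Table 3 is not exhaustive. It omits the pneumococcal qPCR behind a primary endpoint and the total IgA and IgG assays, it has no group columns, and section 144 leaves laboratory detail to an analytical plan that is not among the documents. That plan may already cover Group B. This weakens any inference from the table's silence on other days, but for DNA the table is not silent: it names one draw.

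Third, the DNA entry has blank visit and sample cells because of the page break. Assigning it to day 2 blood is therefore an inference, though its position leaves little room for another.

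Fourth, a reader might infer that objective (xi) as a whole loses 43% of its sample. It does not. Day 2 blood data exist only in Groups A and D, so the analysis of genotype against early innate blood measures loses nobody. Nor are the 35 azithromycin children brought in by this discrepancy. They are in the 255 as well, and only their share changes, from 35/255 = 14% to 35/145 = 24%.

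**Conclusion.** The point holds as a conflict between a stated number and the schedule meant to deliver it. Followed as written, Table 3 yields DNA from 145 children, not 255. Analyses of day 21 outcomes lose 110 of 255 (43%), and analyses of day 7 cellular responses have no genotyped children instead of up to 110. Day 2 blood analyses are intact. This rests on reading the split row of Table 3 as day 2 blood, and on planned group sizes.

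Two stronger readings should be resisted. One is that only 145 children will be, or were, genotyped: the documents report no genotyping numbers, and DNA could be taken from a draw Group B already gives. The other is that the objective becomes underpowered: it has no power target to miss. The change from 0.43 to 0.57 SD describes precision under the assumptions listed and is not a failure against the plan. The objective is exploratory, and no primary endpoint depends on it. The repair is nevertheless more than clerical, because it decides whether a Group B aliquot is set aside at all.

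**What to change.** Reconcile Table 3 with section 101. Keep DNA extraction on day 2 blood for Groups A and D, and add host DNA extraction for Group B to the day 7 blood row or to another draw that Group B already gives. Make the matching change in the laboratory procedure. The stated 255 can then be reached, subject to attrition and missed visits, and genotype can be related to day 7 cellular data in up to 110 children.

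The day 7 row is the lighter choice. It lists three assays, all flow cytometry, whereas the day 0 blood row already lists six. Section 85 puts serum tubes last when volume is short, so moving DNA to day 0 for every group would load the fullest sample although only Group B needs a change.

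The cost is one table entry, one procedure edit and a small aliquot of an existing Group B sample. No extra bleed is needed.
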